### Statistical analyses

#### Baseline characteristics

We will examine rates of ineligibility. Demographic and clinical characteristics will be summarized using descriptive statistics.

#### Primary analyses

##### Comparison of DBT-6 versus DBT-12

Analyses will be conducted at the end of treatment and at the end of follow-up. No interim analyses are planned. The outcome analyses will be conducted on an intention-to-treat basis. The primary outcomes, frequency and severity of suicide and self-harm behaviours, are both expected to have a skewed distribution. The count nature of the self-injury frequency variable, as well as the self-injury severity ratings, are integers bounded by zero. As well, given the dependencies of the observations over time and individual variability, our primary analyses will employ a multilevel random effects Poisson growth curve model. The occasion level random effects will capture secondary over-dispersion due to the heterogeneity of observations within participant self-injury reporting [88, 90]. These random effects will follow a log-normal distribution [91], and will reduce or eliminate the disturbance effects associated with the differences between rates and forms of specific, within individual, self-harm that can bias estimates of true self-harm rates.

Specific tests of our primary hypotheses (non-inferiority tests of equivalence and post hoc comparisons of difference) will be model-based [92] using contrasting means and regression coefficients. Evaluation of model fit will be provided by statistical indices including Akaike’s Information Criteria (AIC) and Bayesian Information Criteria (BIC) and likelihood ratio tests. To perform the comparison of self-injury outcomes at post-treatment (our primary research interest), 1-sided non-inferiority t-tests of the marginal means will be performed. If missing data are at moderate levels or are related to a specific set of covariates or outcome, we will compare multiple imputation [93], growth curve analysis [94], and instrumental variables analysis [95] since no one technique is demonstrably superior [96]. We will also examine differences in sites and therapist characteristics that may be evidenced in treatment outcomes.

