#### Comparison of DBT-6 and DBT-12

The treatment conditions are comparable on all factors except for length of treatment. Both treatment conditions involve all four treatment components, and an equal number of treatment hours per week. In order to control for hours of therapy received, participants are expected to not engage in other primary psychosocial treatments. Further, to control for possible confounding effects of therapist characteristics, therapists across the 2 conditions are matched on a number of factors including expertise, training in DBT, and availability of supervision.

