#### Treatment dropouts

Consistent with the DBT treatment protocol, participants who fail to attend four consecutive scheduled individual or group sessions are discontinued from treatment and will be considered dropouts.

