### Sample size and power analysis

The study was designed to test whether DBT-6 is not inferior to DBT-12 (an established treatment). The estimate of the sample size required for a non-inferiority test was based on the effect sizes from prior DBT RCTs [30, 62]. Post-treatment suicide and self-harm estimates over 4 months were 2.26 episodes for DBT-6 and 0.73 for DBT-12 (SD_pooled_ = 4). We expected no significant differences between the DBT-6 and DBT-12 conditions in terms of reductions in the frequency and severity of self-injury episodes at 1 year. We therefore defined our delta, the clinically significant range of indifference for our non-inferiority trial, as a difference in outcomes of 1.53 (SD = .04) episodes in the frequency of self-harm episodes at post-treatment. To achieve this maximum of 1.53 or less in the difference of self-injury rates with adequate power (α = .05; 1 - β = .80), 85 participants per group are required to show non-inferiority of treatment. Allowing for a 30% dropout rate, we will recruit 120 participants per group. The sample size calculation also addresses the necessary power for secondary analyses, given that the sample size required for null hypothesis significance testing is typically less than those required for non-inferiority [89].

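### Only intention-to-treat is named for a non-inferiority test between arms that differ in treatment length, and no missing-data method is named as deciding

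*Protocol article*

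**What the plan says.** The objective is stated under Sample size and power analysis: "The study was designed to test whether DBT-6 is not inferior to DBT-12 (an established treatment"). The margin is set there "as a difference in outcomes of 1.53 (SD = .04) episodes in the frequency of self-harm episodes at post-treatment", and the recruitment target follows: "Allowing for a 30% dropout rate, we will recruit 120 participants per group".

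Under Primary analyses, Comparison of DBT-6 versus DBT-12, the article says "The outcome analyses will be conducted on an intention-to-treat basis". The primary model is a Poisson growth curve model with random effects, and non-inferiority is judged by one-sided tests of its marginal means. If missingness is moderate, or is associated with covariates or the outcome, "we will compare multiple imputation [93], growth curve analysis [94], and instrumental variables analysis [95] since no one technique is demonstrably superior [96"].

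Three other places bear on this:
- Treatment dropouts: "participants who fail to attend four consecutive scheduled individual or group sessions are discontinued from treatment and will be considered dropouts". Dropout here means stopping treatment.
- Comparison of DBT-6 and DBT-12: the two conditions match in everything but duration, and "participants are expected to not engage in other primary psychosocial treatments".
- Attrition and treatment implementation: completion, dropout timing and adjunctive treatment are to be described and compared between arms. None of this is linked to the non-inferiority conclusion.

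**The concern.** The two arms are meant to deliver the same weekly treatment until month 6. A DBT-12 patient who stops by then has received no more DBT than a DBT-6 completer, so that patient contributes little to the contrast under test. In a superiority trial such dilution works against the claim. In a non-inferiority trial it can work for it. Intention-to-treat is a sound basis for the decision, but with nothing beside it a reader cannot tell a true absence of difference from one produced by early discontinuation.

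The missing-data sentence adds a second weakness. Its trigger is undefined and depends on the data. It opens a comparison of three techniques, one of which (growth curve analysis) is the family of the primary model itself, and it does not say which result stands if they disagree. Instrumental variables analysis is listed with no instrument and no target.

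The Discussion says that confirmed hypotheses could encourage investment in briefer programmes, so the robustness of a non-inferiority claim matters.

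**Working it through.** **Inputs.** Margin 1.53; SD 4, from "Post-treatment suicide and self-harm estimates over 4 months were 2.26 episodes for DBT-6 and 0.73 for DBT-12 (SD_pooled_ = 4"); alpha 0.05; power 0.80; 85 evaluable and 120 recruited per group; 30% dropout allowance (all from Sample size and power analysis). The one-sided test comes from Primary analyses.

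**The plan's own figure.** n = 2 × SD² × (z₀.₉₅ + z₀.₈₀)² / margin² = 2 × 16 × (1.645 + 0.842)² / 1.53² ≈ 84.5, so 85 per group. This matches the article at one-sided 0.05. For dropout, 85 / 0.70 = 121.4, or 122. The stated 120 leaves 120 × 0.70 = 84, with power 0.798. The sample size contains no material arithmetic error.

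**Dilution, illustrative.** Assumptions:
- the true excess among adherers is exactly 1.53;
- a share d of each arm stops early, with the same mean outcome in both arms;
- all 120 per arm have outcomes.

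The intention-to-treat difference is then (1 − d) × 1.53. The standard error is 4 × √(2/120) = 0.516. The chance of claiming non-inferiority is Φ((1.53 − difference) / 0.516 − 1.645).

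| d | ITT difference | Chance of claim |
|---|---|---|
| 0% | 1.530 | 0.050 |
| 10% | 1.377 | 0.089 |
| 20% | 1.224 | 0.146 |
| 30% | 1.071 | 0.225 |

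An 85-per-arm version of the last row gives 0.185. It is not used here, because it first removes the 30% as lost patients and then dilutes the remainder by 30% again.

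**Direction under differential dropout.** Take adherer means of 2.26 (DBT-6) and 0.73 (DBT-12), and assume a mean of 4 for dropouts.
- 45% dropout in DBT-6 and 15% in DBT-12: (0.55 × 2.26 + 0.45 × 4) − (0.85 × 0.73 + 0.15 × 4) = 3.043 − 1.221 = 1.82. The chance of a claim is 0.014.
- 15% and 45%: (0.85 × 2.26 + 0.15 × 4) − (0.55 × 0.73 + 0.45 × 4) = 2.521 − 2.202 = 0.32. The chance of a claim is 0.76.

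**What a both-must-succeed rule would do.** This was simulated with 84 completers and 36 dropouts per arm and uninformative adherence. Requiring both intention-to-treat and per-protocol success gives a claim rate of about 0.047 when the excess among completers is 1.53. Power at a true difference of 0 is about 0.785, against 0.906 for intention-to-treat alone with 120 per arm.

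**The case against.** The strongest reply is that intention-to-treat answers the question the trial asks: what follows from assigning 6 rather than 12 months. For that question a diluted difference of 1.07 is the true difference and lies inside the margin, so claiming non-inferiority is no error. This stands. The inflated rates apply only to the effect of treatment received, and intention-to-treat should stay the deciding analysis.

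Four stronger readings are tempting, and the document does not support them:
- **That no adherence-based analysis exists.** This is a condensed article. A supportive analysis set may be in the full protocol or SAP, which are not shown.
- **That poor retention necessarily favours DBT-6.** The differential scenarios above show the difference moving either way. The article also plans to examine completion, dropout timing and adjunctive treatment, which would expose an imbalance, though it would not adjust the test.
- **That there is no primary analysis, or that instrumental variables are simply misplaced.** The Poisson growth curve model is named as primary, and the three techniques are conditional and listed in advance. Instrumental-variable methods can also address non-ignorable missingness. The fair criticism is that the instrument, the target and the rule for deciding among the three are not given.
- **That the 30% is the expected non-adherence.** The sample size section uses it to inflate the number recruited, that is, as loss of evaluable patients, while the dropout section defines dropout as stopping treatment. Which is meant is unclear.

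Which technique governs is ordinarily settled in an SAP. Here, however, the article itself says the choice will be left to a comparison, and that sentence needs correcting wherever the detail is placed.

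**Conclusion.** The point holds in a limited form. The article names only intention-to-treat for a non-inferiority decision between arms that differ only in length, and it leaves open which of three techniques decides when data are missing. Under equal early discontinuation of 10% to 30%, the chance of claiming non-inferiority when the excess among adherers equals the margin rises from 5% to about 9% to 22%. That range rests on complete outcomes for 120 per arm, equal mean outcomes among those who stop in either arm, and a target of treatment received rather than treatment assigned. The documents give neither the rate nor the timing of non-adherence, so the range shows sensitivity and is not a forecast. The change is worth making, but it does not invalidate the design or the sample size.

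**What to change.** 1. State that the intention-to-treat Poisson mixed model is the single deciding analysis, whatever the level or pattern of missingness.
2. Add a pre-specified supportive adherence-based analysis, not co-primary. It could be an instrumental-variable estimate with randomisation as the instrument for DBT received, a per-protocol set built on the article's own four-session dropout rule, or both. A rule that both must succeed is not advised, since it would take power from about 0.906 to 0.785, below the planned 0.80.
3. Do not exclude patients from the supportive analysis for seeking other therapy after DBT-6 ends. They are plausibly those doing worst, and removing them could flatter DBT-6. Report that uptake by arm from the Treatment History Interview (THI-2).
4. Replace the three-way comparison with multiple imputation that shifts imputed DBT-6 outcomes in the unfavourable direction, and report the shift at which non-inferiority is lost.

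The cost is a little extra analysis on data already being collected. Any per-protocol set carries some selection bias, partly because the dropout rule operates for twice as long in DBT-12. If the analyses disagree, the interpretation has to be more cautious.

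### Once missing data reach an undefined moderate level, or are related to covariates or outcome, the protocol stops saying which analysis decides non-inferiority

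*Protocol article*

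**What the plan says.** All references are to the protocol article.

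- **Primary model** (Primary analyses, Comparison of DBT-6 versus DBT-12): "our primary analyses will employ a multilevel random effects Poisson growth curve model".
- **Test** (same section): for the post-treatment comparison, described as the main research interest, "1-sided non-inferiority t-tests of the marginal means will be performed".
- **Population** (same section): "The outcome analyses will be conducted on an intention-to-treat basis".
- **Missing-data rule** (same section, after the above): the condition is "If missing data are at moderate levels or are related to a specific set of covariates or outcome", and the consequence is "we will compare multiple imputation [93], growth curve analysis [94], and instrumental variables analysis [95] since no one technique is demonstrably superior".
- **Margin** (Sample size and power analysis): delta is given "as a difference in outcomes of 1.53 (SD = .04) episodes in the frequency of self-harm episodes at post-treatment".
- **Dropout allowance** (same section): "Allowing for a 30% dropout rate, we will recruit 120 participants per group".
- **Meaning of dropout** (Treatment dropouts): "participants who fail to attend four consecutive scheduled individual or group sessions are discontinued from treatment and will be considered dropouts".

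**The concern.** A non-inferiority claim rests on one confidence bound set against one margin. The missing-data rule produces three results on the primary question, and the reason it gives denies priority to any of them. Growth curve analysis, the primary method a few sentences before, is listed second of three. The rule sets no threshold for moderate missingness, names no deciding method, and does not say what follows if the three disagree.

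Whether the second trigger applies can be judged only after looking at the data. In a borderline trial, the choice of deciding analysis could then be made with the results in view, and the stated alpha of .05 would no longer describe the procedure.

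The three methods may also not estimate the same thing. If the instrumental-variable analysis uses randomisation as an instrument for treatment received, it generally targets an effect of treatment received and not the intention-to-treat effect that the same section promises.

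**Working it through.** **1. Reproduce the plan's own figures.** Inputs from Sample size and power analysis: margin 1.53, pooled SD 4, true difference 0, one-sided alpha .05, power .80.

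n per group = 2(1.645 + 0.842)² × 4² / 1.53² = 84.5, rounded up to **85**, as stated. (The SD of .04 printed beside the margin cannot be the one used; only 4 reproduces 85. One-sided .025 would give 108.)

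Dropout: 85 / 0.70 = 121.4, so 122 against the stated 120. In reverse, 120 × 0.70 = 84 evaluable per group. The standardised margin is 1.53 / (4 × √(2/84)) = 2.479, and power is Φ(2.479 − 1.645) = .798. The design figures hold together at a one-sided .05.

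**2. Could the condition be met?** The allowance of 30% is 0.30 × 120 = 36 per group, treated in the sizing as not contributing to the 85 needed. That is not a missing-outcome rate, since dropout is defined by missed therapy sessions and assessments can continue. It shows only that substantial loss was provided for. The second trigger, missingness related to covariates or outcome, can be met at any rate of loss.

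**3. What would choosing among three results do to the error rate?** Suppose DBT-6 is worse by exactly the margin, and each of three tests is valid at one-sided .05 and targets the same quantity. With a common correlation ρ between the test statistics, the chance that at least one passes is

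1 − ∫ φ(u) Φ((1.645 − √ρ·u) / √(1 − ρ))³ du.

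With independent tests this is 1 − 0.95³ = .143. The documents give no correlation, so ρ is an assumption:

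| Assumed ρ | At least one of three passes |
|---|---|
| .99 | .059 |
| .95 | .071 |
| .90 | .080 |
| .88 | .083 |
| .50 | .118 |

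Analyses of largely the same observations should be highly correlated, so the rows from .99 to .88 are the relevant ones. The .50 row only shows how the figure behaves when agreement is poor.

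**4. How often would the verdicts differ?** With 84 per group and a true difference of zero, the same model gives conflicting verdicts among the three in 4.8% of trials at ρ = .99, 10.7% at .95 and 15.1% at .90. These are the cases in which the missing ranking would matter even though the treatments are equally effective.

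**The case against.** The strongest reply is that a deciding analysis is named. The Poisson growth curve model is called primary, and the later sentence says only that techniques will be compared. It does not say that the primary model is replaced, that each technique gets its own non-inferiority test, or that the verdict may be picked from among them. On this reading the comparison is a robustness check, and the ranking of methods belongs in an analysis plan that is not shown.

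Part of this stands. The lenient reading is possible, and an analysis plan may settle the matter. But the text does more than stay silent: it gives a reason that puts the three methods on an equal footing. Where the article means a sensitivity analysis it says so, as for the SF-36 under Health economic analyses; that label is absent here.

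Two stronger readings are tempting and are not supported:

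- *The plan itself expects missing data at the triggering level.* It forecasts no missing-outcome rate. The 30% is an allowance for dropout, dropout means leaving treatment, and under intention-to-treat those patients may still be assessed.
- *The plan sets up three primary results from which the best will be taken.* Nothing in the document says that the favourable result will be chosen. The error rates above describe what would happen if it were.

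**Conclusion.** The concern holds as a badly fixed rule. Under its plain wording the named primary analysis loses its priority once the missing-data condition is met, and the document does not say which result then decides non-inferiority. The condition is plausible but not certain.

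The size is modest: one-sided error at the margin of about .06 to .08 in place of .05. This rests on four assumptions: the favourable result is chosen, each test is valid at .05, all three target the same quantity, and their correlations lie between .99 and .88. If the instrumental-variable analysis targets a different effect, the calculation does not cover it, and the need to say which analysis decides is greater. The trial is not invalidated. This should be corrected before the final analysis, with medium confidence, because a lenient reading exists and an unseen analysis plan may already resolve it.

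**What to change.** Replace the missing-data sentence with a rule to this effect:

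- The Poisson growth curve model, fitted to all observed assessments of all randomised patients, decides non-inferiority whatever the level or pattern of missing data.
- Multiple imputation is a sensitivity analysis, preferably also run with imputed DBT-6 outcomes shifted unfavourably, to show how far the conclusion depends on the missing-data assumption.
- Any instrumental-variable estimate is supportive only.
- Neither can replace the deciding result; disagreement is reported as a limit on its robustness.

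The first and last items resolve the ambiguity by themselves. The shifted imputations are an improvement, not a condition for resolving it. With this rule, no threshold for moderate missingness is needed to identify the deciding analysis.

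The cost is wording, a little extra programming and no new data. The article describes follow-up as still running, so the change can precede the final analysis. The downside is that the analysts lose the freedom to switch method after seeing the missing-data pattern.

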### Study setting and recruitment

The study is being conducted at two sites, the BPD Clinic at the Centre for Addiction and Mental Health (CAMH) in Toronto, Ontario, and the Personality and Emotion Research Laboratory in conjunction with the DBT Centre in Vancouver, British Columbia. Of the 240 participants, 160 were enrolled in Toronto and another 80 participants were enrolled at the Vancouver site. Participants were drawn from existing treatment or research wait-lists at the respective sites, through advertisements at hospitals, universities, and health service centres, and via word of mouth referrals from clinicians seeing potentially appropriate patients.

Prospective participants were pre-screened on the phone by a research assistant. The research assistant described the study, explained the screening process, and informed potential participants that if found eligible, they would be randomized to either 12 or 6-months of DBT. If the individual was interested, the research assistant conducted a telephone screen to gather information pertinent to inclusion and exclusion criteria. Individuals who met eligibility criteria were invited to attend an in-person assessment session to determine their eligibility. The in-person assessment was conducted by trained study assessors, who were responsible for obtaining prospective participant consent to participate in the trial. These assessors were also responsible for administering structured interviews and tests that focused on inclusion/exclusion criteria. If the participant was deemed eligible for participation, the interview continued to include structured diagnostic interviewing of Diagnostic and Statistical Manual-IV Axis I and II disorders. The in-person assessment, conducted over the course of 2 days included laboratory measures of attention and implicit associations of emotion regulation with self-harm and the completion of self-report questionnaires. All procedures were approved by CAMH and SFU research ethics boards.

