#### Randomization

Individuals who provided informed consent and were eligible were informed of the treatment arm to which they were assigned by each site’s coordinator after the baseline assessment. The allocation scheme was developed in order to maintain blindness and random assignment, while minimizing wait-list time and avoiding unfilled slots in either treatment arm. The allocation scheme used variable block sizes with permutations of 4 and was generated by the statistician. A research assistant then put the allocation scheme into a series of consecutively numbered white, opaque, sealed envelopes (numbered 1 to n, where n is the study site sample size). When there was a minimum of 1 opening per each of the 2 treatment conditions at either treatment site, the research coordinator opened the next randomization envelope, which revealed participant assignment to either 6-months (DBT-6) or 12-months (DBT-12) of DBT. Randomization was conducted independently at each site.

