### Assessments

Over the course of the study (i.e., 6 or 12 month treatment and follow-up phase), participants are being assessed at 9 time points: pretreatment, 3, 6, 9, 12, 15, 18, 21 and 24 months. Outcome measures are the same as those used in previous RCTs of DBT [27–30, 61, 62], allowing for comparability with previous outcomes. The measures are described below, and Table 1 summarizes the schedule of measures.

**Table 1 Tab1:** Summary of measures

Domain	Report type	Outcome Variable	Measure	Screen	Baseline	3 months	6 months	9 months	12 months	15 months	18 months	21 months	24 months	Post session 1–4	Monthly
Suicide/Self-Harm	Self-Report	Suicidal Ideation	Beck Scale for Suicide Ideation (BSS)		•	•	•	•	•	•	•	•	•		
	Interview	Lifetime Suicide and Self-Injury	Lifetime Suicide Attempt Self-Injury Interview (LSASI)		•										
		Suicide and Self-Injury (past 3 months)	Suicide Attempt Self-Injury Interview (SASII)		•	•	•	•	•	•	•	•	•		
Symptoms	Self-Report	Depression	Beck Depression Inventory-II (BDI-II)		•	•	•	•	•	•	•	•	•		
		Impulsivity	Barratt Impulsiveness Scale-11 (BIS-11)		•	•	•	•	•	•	•	•	•		
		Borderline Personality Disorder (BPD)	Borderline Symptom List-23 (BSL-23)		•	•	•	•	•	•	•	•	•		
		Emotion Regulation Difficulties	The Difficulties in Emotion Regulation Scale (DERS)		•	•	•	•	•	•	•	•	•		
		Interpersonal Problems	Inventory of Interpersonal Problems-64 (IIP-64)		•	•	•	•	•	•	•	•	•		
		Non-Suicidal Self-Injury	Inventory of Statements About Self-Injury (ISAS)		•										
		Post-Traumatic Stress Disorder	PTSD Checklist for DSM-5 (PCL-5)		•	•	•	•	•	•	•	•	•		
		Psychiatric Symptom Distress	Symptoms Checklist-90-Revised (SCL-90-R)		•	•	•	•	•	•	•	•	•		
		Anger Experience and Expression	State and Trait Anger Expression Inventory-2 (STAXI-2)		•	•	•	•	•	•	•	•	•		
		Alcohol Use and Related Problems	The Alcohol Use Disorder Identification Test (AUDIT)		•	•	•	•	•	•	•	•	•		
		Drug Use and Related Problems	Drug Abuse Screening Test (DAST)		•	•	•	•	•	•	•	•	•		
		Childhood Trauma	Childhood Trauma Questionnaire Short Form (CTQ-SF)			•									
		Five Dimensions of Personality	The NEO Five Factor Personality Inventory Short Form (NEO-SF)		•										
Functioning	Self-Report	Social Functioning	Social Adjustment Scale Self-Report (SAS-SR)		•	•	•	•	•	•	•	•	•		
		Medical Outcome	Medical Outcome Score-Short Form (MOS-SF-36)		•	•	•	•	•	•	•	•	•		
		Quality of Life	Euroqol-5D-5 Level (EQ-5D-5 L)		•	•	•	•	•	•	•	•	•		

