### Clinical outcomes

#### Primary outcome

The primary outcome is the frequency and severity of self-injurious episodes, measured by the Suicide Attempt Self-Injury Interview (SASII [63]). The SASII is a semi-structured interview that measures frequency and medical severity of self-injury and suicide attempts and is administered by trained assessors at all assessment points to measure self-injury over the previous 3-month assessment interval.

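### The primary model names no site or therapist term and leaves the role of baseline SASII open; if therapists are nested in arm, the non-inferiority interval would be too narrow

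*Protocol article*

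**What the plan says.** All references are to the protocol article.

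- **Allocation.** The Randomization section states: "Randomization was conducted independently at each site". Study setting and recruitment gives the stratum sizes: "Of the 240 participants, 160 were enrolled in Toronto and another 80 participants were enrolled at the Vancouver site".
- **Baseline outcome.** Under Assessments, "participants are being assessed at 9 time points: pretreatment, 3, 6, 9, 12, 15, 18, 21 and 24 months". Under Primary outcome, the SASII "is administered by trained assessors at all assessment points to measure self-injury over the previous 3-month assessment interval". Table 1 also marks the SASII at baseline, so a pretreatment count exists for the primary variable.
- **Primary model.** Under Primary analyses, "our primary analyses will employ a multilevel random effects Poisson growth curve model". The reasons given are dependence over time and variation between individuals, and occasion-level random effects are added for over-dispersion. For the post-treatment comparison, which the article calls its main interest, "1-sided non-inferiority t-tests of the marginal means will be performed".
- **Site and therapist.** In the same section: "We will also examine differences in sites and therapist characteristics that may be evidenced in treatment outcomes". The section on attrition and treatment implementation adds site and therapist looks at participant characteristics, implementation and dropout.
- **Who treats whom.** The Interventions section says that "therapists across the 2 conditions are matched on a number of factors including expertise, training in DBT, and availability of supervision". It does not say whether a therapist sees patients of one arm or of both.

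**The concern.** Site defined the randomisation strata, so the primary analysis should carry it. The article gives it, like therapist characteristics, a separate exploratory role. Looking at site and therapist differences afterwards does not change the standard error of the primary contrast.

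Hypotheses 1a and 1b are about reductions in self-harm, while the post-treatment test compares marginal means. Having a pretreatment occasion in a growth curve does not by itself adjust that contrast. If the baseline intercept is free in each arm, a chance difference in a skewed count carries through to the post-treatment means. A common baseline mean or a baseline covariate removes it. The article fixes neither.

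Patients who share an individual therapist may have correlated outcomes. If therapists are nested in arm and the model ignores this, the standard error of the arm difference is too small. In a non-inferiority trial that error favours declaring the shorter treatment acceptable.

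**Working it through.** **1. The stated sample size.** Inputs from Sample size and power analysis: margin 1.53, pooled SD 4, alpha 0.05, power 0.80. The one-sided reading comes from Primary analyses. The true difference is taken as 0.

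n = 2 × (1.645 + 0.842)² × 4² / 1.53² = 84.5, so **85 per group**, as stated. This is a plain two-sample calculation. It contains no site, baseline or therapist term and no design effect.

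**2. What the model description covers.** For the primary model the article names time, person and occasion. Elsewhere it mentions adjustment where it intends it: the cost regression adjusts for confounders, and the predictor analyses are growth models with covariates. Site and therapist appear in the primary section only as things to examine.

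**3. Site.** The share of outcome variance due to site (R²) is not given; 0.01 to 0.05 is assumed. With SD = 4 × √(1 − R²), the required n is 84 at R² = 0.01 and 81 at R² = 0.05, against 85. The gain is small. Leaving site out makes the interval slightly too wide, not too narrow.

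**4. Baseline.** The article gives no baseline SD and no baseline-to-outcome correlation. As a rough linear-scale illustration, borrow the post-treatment planning SD of 4 for baseline, take the 120 per group recruited, and assume a correlation of 0.3 to 0.5:

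- SE of the baseline difference between arms = 4 × √(2/120) = 0.52 episodes.
- 95% range of chance imbalance = ±1.96 × 0.52, about ±1.0 episode.
- An imbalance of 1.0 moves an unadjusted post-treatment contrast by 0.3 to 0.5 episodes, which is 20% to 33% of the 1.53 margin.

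An unadjusted standard error already contains this variation, so it is avoidable noise and not an inflated error rate. It arises only if the arms have free intercepts.

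**5. Therapist clustering, if nested in arm and ignored.** Assumed: m = 8 patients per therapist and intraclass correlation (ICC) 0.02 to 0.10. Neither is in the article. Design effect DE = 1 + (m − 1) × ICC; actual one-sided error = 1 − Φ(1.645/√DE); correct interval width relative to the naive one = √DE.

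| ICC | DE | One-sided error | √DE |
|---|---|---|---|
| 0.02 | 1.14 | 0.062 | 1.07 |
| 0.05 | 1.35 | 0.078 | 1.16 |
| 0.10 | 1.70 | 0.104 | 1.30 |

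With m = 6 the error is 0.058 at ICC 0.02 and 0.071 at ICC 0.05.

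**6. Power under the same clustering, 85 per group.** The standardised margin is 1.53 / (4 × √(2/85)) = 2.494.

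- Clustering ignored: Φ((2.494 − 1.645)/√DE) = 79% at DE 1.14 and 74% at DE 1.70.
- Clustering modelled: Φ(2.494/√DE − 1.645) = 76% and 61%.

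The lower pair is the power of the valid test. Clustering itself causes that loss; leaving the term out does not.

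**The case against.** The strongest reply is that the article lists no fixed effects at all, so it neither includes nor excludes these terms, and a covariate list often sits in a fuller document that is not shown. That stands against any claim that the terms are known to be absent. It does not remove the point, because the article does describe the structure of the primary model and gives site and therapist a different role.

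Several stronger readings are tempting and not supported:

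- **That baseline is ignored.** The SASII has a pretreatment occasion and the model is longitudinal, so baseline is plausibly the first point of the curve. Tests on regression coefficients are also foreseen, so change over time may be tested too. What is open is how baseline enters the marginal-mean contrast.
- **That baseline adjustment is worth a known number of patients.** Dividing 85 by 1 − ρ² for ρ of 0.3 to 0.5 gives 93 to 113. That compares a covariate-adjusted linear analysis with a post-treatment-only test. The plan uses neither, so the gain is not established.
- **That therapist clustering certainly biases the test.** Nesting, caseload and ICC are all unstated. Matching of therapists across conditions suggests separate therapists but does not say so. With therapists treating both arms, the inflation in step 5 largely does not apply.
- **That the omissions together misstate the interval in one direction.** Leaving out site or baseline tends to widen it, which is conservative for non-inferiority. Leaving out nested therapists narrows it. The net direction is unknown.

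**Conclusion.** The point holds as a worthwhile change to the specification of the primary model. It is not a demonstrated error in the result or in the sample size. Site and baseline adjustment are improvements with no real downside; the site gain is small, and the baseline gain is modest and cannot be sized from the article. The therapist term matters most, because its omission could make non-inferiority too easy to declare: about 6% to 10% one-sided error in place of 5%, conditional on nesting in arm, 8 patients per therapist and ICC 0.02 to 0.10, all assumed. A reader might infer from these figures that 85 per group is wrong. The article's inputs reproduce it exactly, and nothing in the article shows that clustering is present at a size that would overturn it.

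**What to change.** Before the analysis, fix the following in the primary Poisson mixed model:

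1. Site as a fixed effect.
2. Both arms constrained to a common baseline mean, with the pretreatment SASII as the first occasion; alternatively, the baseline SASII count as a covariate.
3. A statement of whether therapists are nested in or crossed with arm, and a random effect for individual therapist that reflects that structure.
4. The post-treatment marginal-mean difference and its one-sided test derived from this model.

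The planned site and therapist comparisons can stay as descriptive additions.

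The cost is model specification only. Site and baseline SASII are already recorded, and the therapist-patient pairing must be known because adherence sessions are sampled by pair. The therapist term may widen the interval, by roughly 7% to 30% under the assumed values if therapists are nested in arm. That is the price of a valid error rate.
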